### Sample size calculation

This study draws on findings from a previously published clinical observational trial on the application of DPS for post-stroke shoulder pain (15). Sample size estimation was performed using G*Power 3.1 software. The significance level (*α*) was set at 0.05, *β* at 0.20, and statistical power (1−β) at 0.80. Based on the method for comparing two groups of equal size and using an effect size (Cohen’s d = 0.91) as reported in the referenced study, the minimum required number of participants was calculated to be 19 per group, totaling 38. To account for an expected dropout rate of 20%, the sample size was increased to 48 participants. This adjustment ensures sufficient statistical reliability and helps maintain the study’s validity despite potential participant attrition.

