### Data analysis

Statistical analyzes will be performed using SPSS version 27.0. All continuous variables will be tested for normality using the Shapiro–Wilk test. Normally distributed data will be expressed as mean ± standard deviation and analyzed using independent sample *t*-tests for between-group comparisons and repeated measures ANOVA for within-group comparisons across time points (baseline, week 2, week 4, and 1-month follow-up). Non-normally distributed data will be reported as medians with interquartile ranges and assessed using the Mann–Whitney U test and Friedman test, respectively. Categorical variables such as gender or stroke type will be analyzed using chi-square tests or Fisher’s exact tests when appropriate. A two-sided *p*-value < 0.05 will be considered statistically significant for all analyzes.

For musculoskeletal ultrasound outcomes, four key indicators will be analyzed: (1) distance from the acromion to the greater tuberosity of the humerus and (2) thickness of the subdeltoid bursa will be treated as continuous variables and analyzed using the same approach as other quantitative measures—independent *t*-tests or Mann–Whitney U tests for between-group comparisons, and repeated measures ANOVA or Friedman tests for within-group changes. (3) Calcifications in the supraspinatus tendon and (4) effusion around the long head of the biceps tendon sheath will be treated as binary variables (presence/absence) and compared between groups using chi-square tests. All ultrasound images will be independently reviewed by two experienced sonographers blinded to group allocation. Inter-rater reliability will be evaluated using Cohen’s kappa for categorical variables and intraclass correlation coefficients (ICC) for continuous variables. Any discrepancies will be resolved by consensus discussion.

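### 19 per group gives 77.9% power, not 80%, for the planned two-sided t-test at d = 0.91; the shortfall is about 2 points and one patient per arm

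*Protocol article*

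**What the plan says.** The protocol article, Sample size calculation, reports a G*Power 3.1 calculation. The error rates are given as "The significance level (*α*) was set at 0.05, *β* at 0.20, and statistical power (1−β) at 0.80". The calculation is described as "Based on the method for comparing two groups of equal size" and as "using an effect size (Cohen’s d = 0.91) as reported in the referenced study". The result is that "the minimum required number of participants was calculated to be 19 per group, totaling 38"; for an expected 20% dropout, "the sample size was increased to 48 participants". This section does not name the statistical test, the number of sides, or the VAS time point to which d belongs.

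The Data analysis section supplies the test. Normally distributed outcomes are compared between groups with independent-samples t-tests, with Mann–Whitney U as the alternative for non-normal data. The criterion is "A two-sided *p*-value < 0.05 will be considered statistically significant for all analyzes".

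**The concern.** A t-test estimates the standard deviation from the sample, and with fewer than 40 patients that costs power which the large-sample formula ignores. A stated minimum of 19 per group for d = 0.91 lies close to the large-sample answer, so it needs checking against the test that will be used. If 19 is too few, the stated power of 0.80 is not reached at the protocol's own effect size and dropout rate, and the sample of 48 built on it is slightly short. A reader would then credit the trial with a little more sensitivity than it has.

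**Working it through.** **Inputs.** From Sample size calculation: d = 0.91, α = 0.05, power 0.80, equal groups, 20% dropout. From Data analysis: independent-samples t-test, two-sided. Two-sidedness is carried over from the analysis section, because the sample size section does not state it.

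**Step 1: reproduce the stated figure.** Two-sided large-sample normal formula:

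n per group = 2 × (z₀.₉₇₅ + z₀.₈₀)² / d² = 2 × (1.960 + 0.842)² / 0.91² = 18.96, rounded up to 19.

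The same approximation puts power at 19 per group at 80.1%. Dropout: 38 / 0.8 = 47.5, rounded up to 48. Both stated numbers are reproduced.

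**Step 2: repeat for the planned t-test.** Power comes from the noncentral t distribution with 2n − 2 degrees of freedom and noncentrality d × √(n/2).

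| n per group | Degrees of freedom | Noncentrality | Power, two-sided |
|---|---|---|---|
| 19 | 36 | 0.91 × √9.5 = 2.805 | 77.9% |
| 20 | 38 | 0.91 × √10 = 2.878 | 80.1% |
| 24 | 46 | 0.91 × √12 = 3.152 | 87.0% |

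The minimum for 80% is therefore 20 per group. Rounding of d does not explain the gap: at d = 0.905 power with 19 per group is 77.5%, and at 0.915 it is 78.4%. At 19 per group, 80% power needs d = 0.934. A one-sided t-test would need 16 per group, so 19 is not the one-sided answer either.

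**Step 3: carry through dropout.** 40 / 0.8 = 50 enrolled, against 48 planned. In the other direction, 48 × 0.8 = 38.4, so about 38 completers and 77.9% power. Retaining 40 of 48 (8/48 = 16.7% lost) gives 80.1%.

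**Step 4: could another test give 19?** With Mann–Whitney sized by asymptotic relative efficiency, 19 per group is the minimum under a two-sided logistic parent distribution and under a one-sided minimum-efficiency setting. Under a two-sided normal parent it is 21. The article mentions none of these settings.

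**Step 5: effect of adjusting for baseline VAS.** If d is standardised by the SD of the week-4 score, and the baseline to week-4 correlation is r, the residual SD falls by √(1 − r²). At an assumed r = 0.3 the effective d is 0.91 / √(1 − 0.09) = 0.954. With 38 completers and 35 residual degrees of freedom, power is 79.7% by simulation. Direct calculation, averaging over chance baseline imbalance, gives 80.5%. Both round to about 80%, and a larger r gives more. If d belongs to a change score, this conversion does not apply.

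**The case against.** The strongest reply is that nothing fails under a conventional method. The normal formula gives 19, the dropout step is correct, and the gap to the exact answer is one patient per arm, or 2.1 power points. The 77.9% also applies only if the full 20% is lost. All of this stands and limits the size of the point. It does not make 19 right for a two-sided t-test, which is the test the article plans for normally distributed data.

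A second reply is that the test behind the calculation is unnamed, and that some Mann–Whitney settings do yield 19. This also stands. G*Power was not run for this check, so the most that can be said is that its two-sided t-test would be expected to return 20. A reader might infer that the software was misused or its output misreported; the article does not give enough detail to support that.

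A reader might also infer that d = 0.91 is too optimistic against an active comparator. The article calls its source a clinical observational trial, but that study is not available here and its comparator is unknown, so the documents cannot settle this.

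**Conclusion.** The point holds as a small numerical error. For the two-sided independent-samples t-test in the Data analysis section, 19 per group gives 77.9% power at d = 0.91, and 80% needs 20 per group (50 enrolled at 20% dropout). The shortfall is about 2 points with 38 completers and is gone with 40; if all 48 complete, power is 87.0%.

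The conclusion rests on the article's own d, α and dropout rate, on taking the number of sides from the analysis section, and on the t-test being the test used. It would be tempting to conclude that the trial is materially underpowered or must recruit more patients. The figures above do not support that at the stated effect size.

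**What to change.** Keep 48 enrolled and correct the sample size statement. Suggested content: with a two-sided independent-samples t-test at α = 0.05 and d = 0.91, 38 completers give about 78% power and 48 completers give 87%. Name the test, the number of sides, and the VAS endpoint and time point to which d refers. If a different test was in fact used to obtain 19, say which one and with what settings.

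In addition, analyse the primary VAS outcome by ANCOVA adjusted for baseline VAS, which is already collected. Under the assumptions in the working (d on the week-4 score, r about 0.3), this restores about 80% power with 38 completers without further recruitment. The correlation is not given in the article and should be stated as an assumption.

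A line giving power at smaller effects is optional. With 38 completers and the unadjusted t-test it would read 56% at d = 0.7 and 32% at d = 0.5; both effect sizes are illustrative.

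The cost is one rewritten passage on sample size, one changed line in the analysis section, and a stated power slightly below the one now claimed.

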### Study sample

Participants will be eligible for inclusion if they meet all of the following criteria: (1) aged between 40 and 60 years; (2) diagnosed with a first-ever stroke (ischemic or hemorrhagic), confirmed by cranial CT or MRI; (3) onset of hemiplegic shoulder pain after the stroke, with a Visual Analog Scale (VAS) pain score ≥4; (4) Brunnstrom stage II to V on the affected limb; (5) no significant pre-existing shoulder disorders (e.g., rotator cuff tear, severe osteoarthritis, adhesive capsulitis) confirmed by ultrasound and clinical exam; (6) no severe cognitive impairment (Mini-Mental State Examination score ≥24); and (7) able and willing to provide written informed consent.

Participants will be excluded if they have: (1) subarachnoid hemorrhage; (2) two or more prior strokes; (3) significant shoulder subluxation (≥1 finger-width gap between acromion and humeral head) or flaccid paralysis; (4) clinical deterioration due to recurrent infarct or hemorrhage; (5) severe cardiopulmonary conditions (e.g., acute myocardial infarction, unstable angina, severe arrhythmia, aortic stenosis, pericarditis, malignant hypertension); and (6) other causes of shoulder pain unrelated to stroke, such as cervical spondylosis or referred visceral pain.

### Recruitment strategies

The recruitment plan for this study will rely on the existing resources and clinical collaborations within our hospital. The Rehabilitation Department includes 54 inpatient beds, with approximately 60% occupied by stroke rehabilitation patients, of whom nearly 80% experience post-stroke shoulder pain. This patient base provides a strong foundation for participant recruitment. Physicians, nurses, and physical therapists will actively engage eligible patients and inform them about the study to encourage enrollment. In addition, we have close working relationships with the Departments of Neurosurgery and Neurology, where patients are typically transferred to the Rehabilitation Department for further treatment about 10 days after the acute phase of stroke. This collaboration ensures access to a steady and suitable flow of potential participants.

Recruitment will also involve physician-led patient education, printed posters and advertisements placed in high-traffic hospital areas such as elevators and outpatient departments, and outreach through community healthcare centers to broaden awareness. These strategies are designed to secure the required sample size for the trial.

### Enrollment and the informed consent process

Participants will be enrolled in groups of at least 10 per intervention cycle to support a structured group intervention setting and maintain an equal 1:1 allocation between the two treatment arms. Within 2 weeks prior to the intervention phase, baseline assessments will be conducted for 10 to 20 pre-screened individuals to establish an eligible pool for randomization.

Before any data are collected, the principal investigator (CW) or the research coordinator will initiate the informed consent process. Each participant will receive a written consent form and a detailed explanation of the study. Those who agree to participate will sign the form. Following consent, eligibility will be confirmed based on the predefined inclusion criteria. Once eligibility is verified, the study team will explain the trial procedures in detail to ensure that participants fully understand the nature of their involvement. Completion of these steps finalizes the enrollment process.

### Randomization

Once written informed consent was obtained and baseline assessments were completed, an off-site research assistant performed the randomization using SPSS version 27. Participants were randomly assigned to either the DPS therapy group or the SCTT group. To reduce potential allocation bias, stratified randomization was applied based on time since stroke (in years) and stroke type (ischemic or hemorrhagic).

To ensure allocation concealment, all information regarding group assignment, therapy schedules, and intervention locations was communicated solely through centralized telephone contact, managed by the off-site research assistant. This method kept other study personnel blinded to group assignments and helped minimize bias throughout the intervention phase.

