**Figure 1 fig1:**
[figure not shown]
Study design flowchart: a detailed depiction of participant progression through each stage of the study.

The primary outcome is pain intensity, assessed using the VAS, a widely recognized and validated tool. VAS scores will be recorded at baseline, at 2 and 4 weeks during treatment, and again at a 1-month follow-up after completion of the intervention. Secondary outcomes assess shoulder joint function across four domains. First, ROM will be measured to evaluate mobility of the affected shoulder. Second, the absolute vertical distance difference between the medial superior angle of the scapula on the affected side and the second thoracic spinous process will be recorded. Third, musculoskeletal ultrasound will be used to assess five key indicators: presence of effusion around the long head of the biceps tendon sheath, calcification in the supraspinatus muscle, calcification at the insertion of the subscapularis tendon, subdeltoid bursa thickness (in millimeters), and the distance from the acromion to the greater tuberosity of the humerus. Lastly, the MBI will be used to evaluate overall independence in daily living activities. Covariates include age, sex, body mass index (BMI), stroke type (hemorrhagic or ischemic), and time since stroke onset. All outcome measures will be collected at baseline, 2 weeks, and 4 weeks after treatment begins. A follow-up VAS will be conducted 1 month post-intervention to assess the sustained effects of DPS in relieving post-stroke shoulder pain. The physical function assessments will be performed by trained evaluators blinded to treatment allocation, and data analysis will be conducted by statisticians also blinded to group assignments.

Detailed outcome variables and their classification as endpoints or intermediate measures are summarized in Table 1.

**Table 1 tab1:** Baseline assessment and sequence of trial measurements for primary and secondary outcomes.

	Before-intervention	Mid-intervention	Post-intervention	1-month follow-up
Time (weeks)	**0**	**2**	**4**	**8**
Baseline				
Sex (male/female)	**√**			
Type of stroke (ischemia/hemorrhage)	**√**			
Age, y	**√**			
BMI	**√**			
Time since stroke, y	**√**			
Primary outcome variable				
VAS	**√**	**√**	**√**	**√**
Secondary outcome variables				
Shoulder ROM				
Flexion (0–180°)	**√**	**√**	**√**	
Extension (0–50°)	**√**	**√**	**√**	
Abduction (0–180°)	**√**	**√**	**√**	
Adduction (0–40°)	**√**	**√**	**√**	

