### Study intervention

Both the DPS therapy and SCTT were implemented concurrently to reduce variability caused by seasonal changes in symptom severity. During the four-week intervention phase, participants in both groups received manual therapy according to their assigned treatment. Each group underwent five therapy sessions per week, each lasting 40 min, for a total of four weeks. Participants remained in inpatient rehabilitation during this period, and weekly consultations were held to monitor adherence. The four-week treatment window reflects standard practice in China, where medical insurance typically limits inpatient rehabilitation to this duration.

Participants were instructed not to take nonsteroidal anti-inflammatory drugs (NSAIDs), including celecoxib, or acetaminophen during the trial. Medications such as celecoxib may pose risks for post-stroke shoulder pain patients with a history of cardiac stent placement, as they can impair platelet function and increase cardiovascular risk (7, 16). In cases of severe pain, acupuncture was used as a temporary alternative, integrated into the basic rehabilitation regimen. Routine rehabilitation therapy continued throughout the study to ensure uniformity in care delivery.

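### Time since stroke is a stratification factor in years with no bands, which may not balance recovery phase within the first year, and the stated between-group tests do not adjust for it

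*Protocol article*

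**What the plan says.** The Randomization section reports that "stratified randomization was applied based on time since stroke (in years) and stroke type (ischemic or hemorrhagic"). The two levels of stroke type are written out, but time since stroke has only a unit. Table 1 lists the baseline variable in the same unit: "Time since stroke, y".

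Recruitment strategies names several sources:
- **Department inpatients:** "The Rehabilitation Department includes 54 inpatient beds, with approximately 60% occupied by stroke rehabilitation patients, of whom nearly 80% experience post-stroke shoulder pain".
- **Neurosurgery and Neurology:** "patients are typically transferred to the Rehabilitation Department for further treatment about 10 days after the acute phase of stroke".
- **Outpatient and community routes:** "printed posters and advertisements placed in high-traffic hospital areas such as elevators and outpatient departments, and outreach through community healthcare centers to broaden awareness".

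The criteria under Study sample require a patient "diagnosed with a first-ever stroke (ischemic or hemorrhagic), confirmed by cranial CT or MRI" and set neither a minimum nor a maximum time since onset. Study intervention adds that "Participants remained in inpatient rehabilitation during this period", which covers the four weeks of treatment.

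Study design overview lists stroke type and time since onset among the covariates. Data analysis, however, gives the between-group comparison as an independent-sample t-test or a Mann-Whitney U test and describes no model containing those covariates.

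**The concern.** Stratifying on time since stroke is presumably meant to keep the arms alike in recovery phase. Because eligibility has no time window, stratification is the only design feature that could do this. A unit of years sits awkwardly with a referral stream that arrives within weeks of the event. In whole-year bands, a patient a few weeks after stroke and a patient nine months after stroke share a stratum, so the scheme does not control how each is spread across the arms.

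The analysis as described does not make up for this. An unadjusted test ignores both stratification factors. If those factors are prognostic for VAS, it gives up precision that stratification could have bought. It also leaves any chance imbalance in early recovery time in the treatment estimate. With 24 patients per arm, such imbalances are not rare.

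**Working it through.** **Plan's own figures.** No figure is given for the strata: no cut-points, no number of strata and no distribution of time since stroke. The sample size is needed only for the arm size. The article states 38 evaluable patients and 20% dropout; 38 / 0.80 = 47.5, rounded up to 48, or 24 per arm.

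**Step 1: where the early stream falls on a year scale.** Ten days is 10/365 = 0.027 year. The length of the acute phase that precedes those days is not given. Unless it is very long, these patients are well under one year, and whole-year bands place them all in the lowest one.

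**Step 2: how much of the sample is affected.** This depends on the share q of recruits one year or more after stroke. The share is not given, so both q and a one-year cut are assumptions here. The last column is the hypergeometric chance that, in a 24/24 split not stratified on this cut, the arms differ by 4 or more such patients.

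| q (assumed) | Patients at 1 year or more, of 48 | Chance of arm difference of 4 or more if not stratified |
|---|---|---|
| 0% | 0 | 0% |
| 5% | about 2 | 0% |
| 10% | about 5 | 5% |
| 20% | about 10 | 29% |
| 30% | about 14 | 34% |
| 50% | 24 | 39% |

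At q of 0 to 5% a one-year cut does almost no work. At 20 to 50% it separates a real second group and guards against imbalances that would otherwise be common. In neither case does it separate patients within the first year.

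**Step 3: chance imbalance in a split the scheme does not balance.** Assume an early/later split that divides the 48 patients 50:50 and is not stratified.
- SD of the between-arm difference in share = sqrt(2 × 0.25 / 24) = 0.144, or about 14 percentage points.
- P(gap of 20 points or more) = 2 × (1 − Φ(0.20 / 0.144)) = 2 × (1 − Φ(1.39)) ≈ 0.166.
- The exact value with 24 of 48 patients fixed as early is 0.148.

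Both are near 1 in 6. This is the generic figure for any unstratified 50:50 factor at this sample size.

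**Step 4: what a gap does to the estimate.** If early and later patients differ by δ in mean VAS change, a gap of 0.20 in share shifts the unadjusted arm difference by 0.20 × δ. The documents give no δ. As a yardstick, if δ were as large as the planned treatment effect of 0.91 SD, the shift would be 0.20 × 0.91 = 0.18 SD.

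**Step 5: design against analysis.** Randomization uses two factors, and Study design overview names both as covariates. The between-group tests in Data analysis use neither.

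**The case against.** The strongest reply is that the year wording may be no more than a unit. Decimal years with a cut below one year would separate early from later patients, and a decimal value carries as much information as days. A condensed article may also leave cut-points to the full protocol. This stands, and it is why the point about the strata is conditional on whole-year bands.

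A reader might infer that nearly all recruits are in their first weeks, so that the factor is effectively constant and the stratification is useless. The documents do not support that:
- The ten-day statement concerns one referral stream, introduced as an addition to the existing inpatient base.
- Outpatient and community routes are also named, and no time window excludes patients years after stroke.
- Stroke type still stratifies whatever happens to the other factor.

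A reader might also infer that many sparse year strata upset the 1:1 balance, given that "Participants will be enrolled in groups of at least 10 per intervention cycle". Neither block size nor number of strata is stated, so this cannot be sized. It also conflicts with the premise that nearly everyone falls in one stratum.

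Finally, randomisation remains valid. A chance imbalance is confounding in the realised comparison, not systematic bias, and the listed covariates may be used in an analysis plan that is not shown. That softens the analysis point but does not remove it, because the article does state the between-group tests and they are unadjusted.

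**Conclusion.** The point holds in a limited form. If whole-year bands are used, the stratification cannot balance recovery phase within the first year, and the early-referral stream falls into a single stratum. The inpatient setting makes early patients likely to be frequent, but their share is not documented, so the effect on the whole sample cannot be fixed. Separately from how the bands are read, the stated between-group tests use neither stratification factor and would not correct an imbalance.

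The size is moderate. Under an assumed 50:50 early/later split with 24 per arm, a gap of at least 20 points occurs in about 1 in 6 allocations. Each such 20-point gap moves the unadjusted estimate by one fifth of the early/later difference in VAS change, and the documents do not quantify that difference. The change is worth making because the adjustment costs almost nothing.

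**What to change.** 1. Take the date of stroke onset from the chart and record time since stroke in days or weeks.
2. Make the primary VAS comparison with a model, for example ANCOVA, that includes stroke type and time since stroke for all patients, including those already randomised.
3. State the bands actually used so far and the expected spread of time since stroke across the recruitment routes.
4. If randomisation is still open, stratify the remaining patients on one pre-specified cut within the first year crossed with stroke type (2 × 2 = 4 strata). The Randomization section is written in the past tense, so this step may no longer be available; items 1 to 3 apply regardless.

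The cost is one chart date per patient, a revised list from the off-site assistant for any remaining patients, and one or two model degrees of freedom.
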